## Abstract

**Background:**

Primary dysmenorrhea (PD) is one of the main gynecological complaints in women of child-bearing age, but limited effective treatments are available. Guizhi Fuling Wan (GFW), one of the most widely known traditional Chinese medicine (TCM) formulations, has been commonly used in clinical practice to treat gynecological disorders in China. In recent years, a growing number of studies have shown that GFW is beneficial for patients with PD. However, the quality of evidence is limited, and there are few studies on specific TCM syndromes of GFW for PD. Therefore, we plan to conduct a randomized controlled trial to explore the efficacy and safety of GFW for PD patients with heat-burning blood-stasis syndrome.

**Methods and analysis:**

The clinical study is a randomized, double-blinded, placebo-controlled trial. Eligible patients will be randomly assigned to the GFW group (treated with GFW) and the control group (treated with a matching placebo) in a 1:1 ratio for three menstrual cycles with a 3-month follow-up. The primary outcome will be the mean change of pain intensity measured by the visual analog scale (VAS). The secondary outcomes will include the Cox Menstrual Symptom Scale (CMSS), the Self-rating Depression Scale (SDS), the Self-rating Anxiety Scale (SAS), and the TCM syndrome scale. Adverse events will also be reported.

**Discussion:**

This randomized trial will be the first rigorous study designed to assess the efficacy and safety of GFW in treating PD with heat-burning blood-stasis syndrome. The finding of this study will provide an objective clinical basis for the use of GFW for PD in the future.

**Trial registration:**

Chinese Clinical Trial Registry ChiCTR2000034118. Registered on 24 June 2020

**Supplementary Information:**

The online version contains supplementary material available at 10.1186/s13063-021-05834-0.

## Background

Primary dysmenorrhea (PD) is a common gynecological disorder among reproductive women. It is estimated that 40 to 75% of women may suffer from cramping pain in the lower abdomen, even with associated symptoms such as weakness, diarrhea, nausea, and headache [1–4]. Approximately 75% of reproductive women are affected by PD at some point in their lives. Meanwhile, absenteeism from school and work due to severe PD has been as high as 14%, seriously affecting their quality of life [4, 5]. Currently, the most commonly used clinical pharmacological therapies are non-steroidal anti-inflammatory drugs (NSAIDs) and oral contraceptives [6, 7]. Given that 10–20% of PD patients do not respond to the treatment of NSAIDs and that some patients cannot tolerate their side effects or are unsuitable for their indications [8, 9], alternative therapies have become an important addition for PD treatment, in which Chinese herbal medicine (CHM) has played the essential role. CHM, as an essential part of traditional Chinese medicine (TCM), has been widely used in the clinical treatment of PD, especially in China. GFW is one of the most widely known CHM formulas for the treatment of PD and consists of five herbs, including Cinnamon Twig, Poria cocos, Cortex Moutan, Radix Paeoniae Rubra, and Peach kernel. Originating from ancient simple philosophy and empirical medicine, the effect of GFW has been proven in clinical practice and widely used to treat PD, as well as other gynecological diseases such as endometriosis, uterine fibroids, pelvic inflammation, and mastocytosis [10]. In recent basic researches, GFW’s pharmaceutical ingredient had been shown to suppress uterus contraction, prostaglandin level reduction, and correction of luteal insufficiency, demonstrating the potential of promising drugs for PD [11–13]. It also suggested that the GFW had therapeutic effects on PD rats via the regulation of multiple metabolic pathways [14]. Several clinical trials have also shown promising results and no severe adverse reactions of GFW in the treatment of PD [15–18]. However, the relevant studies were prospective long-term clinical observational studies, while RCTs were rare [19]. A few earlier RCTs followed the 2010 version of the CONSORT standard. They rarely used the latest CONSORT extension for Chinese herbal medicine formulas 2017, which can better ensure the quality and authenticity of TCM researches [20]. In addition, most trials did not diagnose patients with TCM dialectical classification, which is the core of TCM treatment practice [21]. A systematic review suggested that GFW was effective in treating PD. However, the authors concluded that the clinical results in these studies were tentative and should be interpreted with caution due to the lack of quality of the included studies [22]. Therefore, to evaluate the efficacy and safety of GFW for PD with the heat-burning blood-stasis syndrome in a small sample size and to reduce the subjective expectations of the study subjects and investigators, we aim to design a rigorous randomized, double-blinded, placebo-controlled trial.

## Methods

### Design and setting

This study is a randomized, double-blind, and placebo-controlled exploratory trial with two parallel groups. The study is designed using Consolidated Standards of Reporting Trials guidelines Extension for Chinese Herbal Medicine Formulas 2017 (CONSORT CHM Formula) [20] and adhere to the Declaration of Helsinki (2013 version). Meanwhile, we designed the study according to the Standardized Protocol Items: Recommendations for Interventional Trials (SPIRIT) statement [23] (details see Additional file 1). The study protocol has been approved by the Ethical Committee of The Second People’s Hospital of Yichang (No. 2020001) and has been registered at the Chinese Clinical Trials Registry in 2020 (No. ChiCTR2000034118.) (details see https://trialsearch.who.int/Trial2.aspx?TrialID=ChiCTR2000034118 and Additional file 2).

The trial is being conducted at the Second People’s Hospital of Yichang. Participants meeting the inclusion criteria will be randomly allocated to either the GFW group (treated with GFW) or the control group (treated with a matching placebo) in a 1:1 ratio. The total observation period will be 7 months, including a 1-month baseline period, a 3-month treatment period, and a 3-month follow-up period. The intensity of menstrual pain and the acute medication use will be asked to record in dysmenorrhea diaries throughout the trial. Assessments will be conducted at baseline and at 1, 2, 3, 4, 5, and 6 months postmenstrual cycles. The flow chart is shown in Figs. 1 and 2 illustrates the schedule of enrolment, interventions, assessments, and data of participants.

**Fig. 1 Fig1:**
[figure not shown]
Flowchart of the trial

**Fig. 2 Fig2:**
[figure not shown]
Schedule of enrolment, interventions, assessments, and data collection. *CMSS* Cox Menstrual Scale, *SDS* the Self-rating Depression Scale, *SAS* the Self-rating Anxiety Scale, *SF-12* the 12-item Short-Form Health Survey, *AEs* adverse events

### Participants

Potential participants who meet the inclusion criteria but do not meet any exclusion criteria as diagnosed by two TCM gynecologists will be asked to meet face-to-face with a research assistant to discuss the study. Eligible patients interested in participating will undergo a series of condition assessments and safety evaluations. After giving informed consent, they will be randomized into two groups.

### Inclusion criteria

Participants meeting the following criteria will be included: (1) nulliparous women aged 16 to 30 years old; (2) meeting the diagnostic criteria for PD in Chinese Obstetrics And Gynecology (3rd edition); (3) meeting the TCM diagnosis of “heat-burning blood-stasis syndrome”; (4) pain symptoms persisted for 6 months to 15 years; (5) VAS score of menstrual pain ≥ 40 mm for at least three consecutive menstrual cycles; (6) patients with the syndrome of heat burning and blood stasis; and (7) signed informed consent form.

### Exclusion criteria

Participants will be excluded if they meet any of the following criteria: (1) unable to complete or comply with the study; (2) imaging examination suspects secondary dysmenorrhea; (3) pregnancy during the trial; (4) inability to cooperate with the questionnaires due to intellectual or mental disorder; (5) history or presence of clinically relevant severe cardiovascular diseases, liver, kidney dysfunction, or psychiatric disease; (6) treatment of PD with analgesics, antidepressants, or psychotropic drugs in the past month; (7) irregular menstrual cycle (beyond the typical range of 21–35 days); and (8) are participating in the other clinical trials of drugs.

### Recruitment and informed consent

PD patients will be recruited through the gynecology clinic of the Second People’s Hospital of Yichang, media releases from Three Gorges University, and online promotion. A 1-month baseline assessment will be needed before randomization, and two research assistants will visit the gynecology department of the hospital twice a week to identify and invite eligible patients to participate in the study. During the baseline assessment period, subjects who meet the acceptance criteria and agree to join the study will be explained the general study process and the responsibilities of the participants and researchers. In addition, patients will be informed of all details of the study and then sign a written informed consent form, which will also be signed and witnessed by the research assistants. No additional biological samples will be obtained to be stored for use in this study. Sample patient informed consent is seen in Additional file 3.

### Randomization and allocation concealment

Eligible participants will be randomly assigned to either the treatment group or the control group by the simple randomization in a 1:1 ratio. Random numbers are computer-generated using the SPSS Statistics for Windows, version 22.0 (SPSS Inc., Chicago, III., USA) by an independent researcher, who will not be involved in patient care, outcome assessment, data collection, or data analysis. For allocation concealment, the practice is to enclose assignments in sequentially numbered, sealed envelopes. The sealed envelopes cannot be opened unless a new participant is included in the trial and will be kept in a safe place in numerical order until the study is completed. Complete separation from the individuals involved in the steps before enrolment from those involved in the allocation concealment. All patients who agree to participate and meet the inclusion criteria will be randomized. Randomization will be requested by the staff member responsible for recruitment. In return, the clinical center will give a closed opaque envelope with randomization numbers inside. The therapist will open the envelope and will find the treatment to be administered to that patient. The staff member responsible for recruitment will not be allowed to receive information about the group assignment.

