### Blinding

The participants, clinical researchers, outcome evaluators, data manager, and statisticians will be blinded to the treatment allocations during the study. The placebo granule is matched to the GFW granule in color, taste, odor, and outer packaging to ensure that the researchers and patients involved in the study are entirely unaware of the identity of the treatment being given. Blinding will not be disclosed until the end of the study unless a serious adverse event (SAE) occurs and their specific treatment needs to be known to provide emergency assistance. Details of the unblinding, such as the reason and date, will be recorded on a case report form (CRF).

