### Interventions

Participants in the GFW group will receive GFW (herb granule, 30 g per packet) treatment. It has the effect of clearing heat and dispelling dampness, blood circulation, removing blood stasis, and clearing away heat and blood. It consists of five natural herbs: Guizhi (Cinnamon Twig) 6 g, Fuling (Poria Cocos) 6 g, Mudanpi (Cortex Moutan) 6 g, Chishao (Radix Paeoniae Rubra) 6 g, and Taoren (Peach Kernel) 6 g [24]. Participants in the control group will receive a GFW-matched placebo consisting of Maiya (Hordei Fructus Germinatus) without analgesic effects. The dosage form, color, appearance, and packaging of the GFW-matched placebo are consistent with those of GFW in the treatment group [25]. Both granules are provided and quality controlled by Beijing Tcmages Pharmaceutical Co. Ltd. (Beijing, China) and distributed by the Second People’s Hospital of Yichang. All drugs are packaged and labeled uniformly.

According to clinical experience, a total of 3 menstrual cycles were treated, each cycle from 7 days before each menstruation to the 3rd day of menstruation, once in 12 h, 30 g each time for ten days. All the participants will be advised not to take NSAID drugs or COCs for PD during the baseline, treatment, and follow-up periods. However, physical therapies (e.g., hot compress and moxibustion) are allowed if the pain is intolerable and the outcome assessment is not scheduled in the next 48 h [26].

To improve patient compliance with the intervention protocol, patients will be required to record all these treatments and keep the package after each dose. The formula calculates the compliance rate: Compliance rate = (actual dosage/expected dosage) × 100%. Patients with a compliance rate ≥ 80% are considered to have good compliance. In addition, face-to-face compliance reminders will be held at each medication distribution to emphasize dosing instructions, the purpose of treatment, etc., especially for those participants who do not achieve 80% of the compliance rate.

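### Read literally, the envelope procedure tells the therapist which treatment is given, contradicting the double-blind claim; the text must be reconciled, though actual unblinding is not shown

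*Protocol article*

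**What the plan says.** All references are to the protocol article.

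- **Design and setting:** "This study is a randomized, double-blind, and placebo-controlled exploratory trial with two parallel groups".
- **Blinding:** participants, clinical researchers, outcome evaluators, the data manager and the statisticians are all listed as blinded. The placebo is matched "to ensure that the researchers and patients involved in the study are entirely unaware of the identity of the treatment being given".
- **Randomization and allocation concealment:** "the practice is to enclose assignments in sequentially numbered, sealed envelopes". The envelope is then described as a "closed opaque envelope with randomization numbers inside". The next sentence reads: "The therapist will open the envelope and will find the treatment to be administered to that patient". One role is explicitly shielded: "The staff member responsible for recruitment will not be allowed to receive information about the group assignment".
- **Interventions:** "All drugs are packaged and labeled uniformly". Also, "face-to-face compliance reminders will be held at each medication distribution".
- **Primary outcome:** pain intensity on a 0 to 100 visual analog scale, rated by the participant.
- **Data collection and management:** the assessors who complete the case report forms are stated to be blinded to assignment.

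**The concern.** The allocation text describes what an open-label trial with concealed envelopes would do: the recruiter stays ignorant, and the treating person opens the envelope and learns the treatment. That protects allocation concealment, but it does not protect blinding after allocation. The rest of the article claims a double-blind design in which the researchers do not know the treatment.

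What is at stake is the protection of a subjective endpoint. The Background gives reducing the expectations of both subjects and investigators as a reason for the design. If someone who treats participants knows the arm, encouragement or inadvertent disclosure could differ between arms and reach the self-rated pain score through the participant's expectation. A reader of the final report would also be unable to tell which roles were in fact blinded.

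**Working it through.** The documents give no figure for this point, so the check sets the passages side by side.

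1. **Who should be blind.** The list in the Blinding section does not name the therapist separately. The terms clinical researchers, and researchers involved in the study, would naturally cover that role. No exception is stated for it.

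2. **What the envelope holds.** The same section gives two descriptions: assignments ("the practice is to enclose assignments in sequentially numbered, sealed envelopes") and numbers ("closed opaque envelope with randomization numbers inside"). The first reveals the arm. The second need not.

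3. **What the opener learns.** "The therapist will open the envelope and will find the treatment to be administered to that patient" says treatment, not a number or a pack.

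4. **Who is shielded from the contents.** Only the recruiting staff member is named ("The staff member responsible for recruitment will not be allowed to receive information about the group assignment"). A bar on group information fits most naturally with an envelope that carries group information.

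5. **What could keep the opener blind.** The article offers product matching and uniform labels ("All drugs are packaged and labeled uniformly"). Matching hides the arm from a person who sees only the product. It does nothing for a person who has been told the assignment.

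6. **The two readings compared.**

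| | Literal reading | Coded reading |
|---|---|---|
| Envelope reveals | the treatment | a number only |
| Therapist | unblinded | blinded |
| Blinding section | false for this role | stands |
| Allocation section | stands, except for the mention of numbers | wrong where it says the envelope encloses assignments and shows the treatment |

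Neither reading leaves every sentence standing, so a correction is needed in both cases. Only its place and extent differ.

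7. **Route to the primary outcome.** The participant rates the pain score and is stated to be blinded. The assessor is also stated to be blinded. On the literal reading, the remaining path runs from the therapist's knowledge, through the therapist's behaviour, to the participant's expectation and then the rating. That is exposure to bias by an indirect path. It is not evidence that bias occurs.

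8. **Size.** The article gives no expected shift in ratings, so there is nothing to put into a formula.

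**The case against.** The strongest defence is the coded reading. The sentence just before the disputed one says the envelope contains randomization numbers. If that number points to a pack, the therapist can give the right product without knowing the arm, and this agrees with the Blinding section and with uniform packaging. The disputed sentence would then be loose drafting. Kit numbering, code lists and code-break storage are also details that a journal article commonly leaves to the full protocol, so their absence here proves nothing. This defence stands in part: it rules out concluding that the blind is broken. It does not remove the conflict, because the article positively states that assignments are enclosed and that the treatment is found.

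The other safeguards also count. Participants, assessors, the data manager and the statisticians are stated to be blinded, and assessments take place in a separate space. Even on the worst reading, one role is unblinded. One caveat applies: the Discussion concedes subtle differences in odor and taste between placebo and active granules, whereas the Blinding section says they match, so product matching is a weaker second line than claimed.

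A reader might infer more than the documents support:

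- **That the trial is not double-blind.** The coded reading leaves this open.
- **That learning one code would unblind a whole arm.** This presumes a shared group code, and none is described. With individually numbered packs it would not follow.
- **That the therapist dispenses, gives the compliance reminders, permits physical therapies or judges adverse-event relatedness.** The article gives relatedness to investigators, describes no permission step for physical therapies, and does not say who holds the face-to-face reminders. It also does not exclude the therapist from these tasks.
- **That the type I error is inflated by a stated amount.** Any such figure needs an invented shift in ratings. It also needs an assumption about units, because the Sample size section gives its difference of 1 and SD of 1.67 without a unit while the primary outcome is scored 0 to 100.

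**Conclusion.** The contradiction is certain and stands on the face of the text: the allocation section conflicts with the Blinding section and with the double-blind label in Design and setting. That the therapist is actually unblinded is possible but not established, and it depends on what the envelope inserts and packs really show. This is more than missing detail, because a stated rule, if followed, defeats a stated safeguard for the treating role. The possible consequence for the self-rated primary outcome is indirect, and its size cannot be estimated from the documents. The conclusion rests on one assumption: that the therapist is among the researchers whom the Blinding section describes as unaware. It depends on no sample-size, power or alpha figure.

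**What to change.** First establish what the current inserts and packs show. Then make one of two changes.

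- **If the inserts and packs are coded, or can be made so:** replace the disputed sentence and the statement that assignments are enclosed. Suggested content: the envelope holds only a randomisation or kit number; the therapist gives the pack bearing that number; packs are individually numbered in advance from the list and identically labelled; no treatment name or group code appears on insert or pack; the key and the emergency code-breaks are held by the independent researcher who generates the sequence.
- **If the therapist has been or will remain unblinded:** say so, describe how that role is kept apart from participant ratings and outcome assessment, and narrow the blinding claim in Design and setting, in Blinding and wherever it is repeated.

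The cost is small. If the materials are already coded, it is a text amendment with the sponsor and ethics committee approval that the Protocol amendments section requires. Relabelled packs and new inserts are needed only if the current ones reveal the arm, and only for patients not yet randomised. The independent researcher is already in the plan. The Trial status section reports recruitment under way at submission, so a correction cannot restore blinding for patients already allocated under a revealing insert. Any such patients should be acknowledged in the report.

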### Blinding

The participants, clinical researchers, outcome evaluators, data manager, and statisticians will be blinded to the treatment allocations during the study. The placebo granule is matched to the GFW granule in color, taste, odor, and outer packaging to ensure that the researchers and patients involved in the study are entirely unaware of the identity of the treatment being given. Blinding will not be disclosed until the end of the study unless a serious adverse event (SAE) occurs and their specific treatment needs to be known to provide emergency assistance. Details of the unblinding, such as the reason and date, will be recorded on a case report form (CRF).

### Interventions

Participants in the GFW group will receive GFW (herb granule, 30 g per packet) treatment. It has the effect of clearing heat and dispelling dampness, blood circulation, removing blood stasis, and clearing away heat and blood. It consists of five natural herbs: Guizhi (Cinnamon Twig) 6 g, Fuling (Poria Cocos) 6 g, Mudanpi (Cortex Moutan) 6 g, Chishao (Radix Paeoniae Rubra) 6 g, and Taoren (Peach Kernel) 6 g [24]. Participants in the control group will receive a GFW-matched placebo consisting of Maiya (Hordei Fructus Germinatus) without analgesic effects. The dosage form, color, appearance, and packaging of the GFW-matched placebo are consistent with those of GFW in the treatment group [25]. Both granules are provided and quality controlled by Beijing Tcmages Pharmaceutical Co. Ltd. (Beijing, China) and distributed by the Second People’s Hospital of Yichang. All drugs are packaged and labeled uniformly.

According to clinical experience, a total of 3 menstrual cycles were treated, each cycle from 7 days before each menstruation to the 3rd day of menstruation, once in 12 h, 30 g each time for ten days. All the participants will be advised not to take NSAID drugs or COCs for PD during the baseline, treatment, and follow-up periods. However, physical therapies (e.g., hot compress and moxibustion) are allowed if the pain is intolerable and the outcome assessment is not scheduled in the next 48 h [26].

To improve patient compliance with the intervention protocol, patients will be required to record all these treatments and keep the package after each dose. The formula calculates the compliance rate: Compliance rate = (actual dosage/expected dosage) × 100%. Patients with a compliance rate ≥ 80% are considered to have good compliance. In addition, face-to-face compliance reminders will be held at each medication distribution to emphasize dosing instructions, the purpose of treatment, etc., especially for those participants who do not achieve 80% of the compliance rate.

Participants are free to withdraw from the trial if they feel they are not getting better. Also, if they develop a serious illness or a serious adverse event related to the study, allocated interventions will discontinue. Participants can continue to receive health counseling services from clinicians after completing the study. Doctors should offer alternative treatments for patients who have completed the trial without remission, such as combined conservative treatments like acupuncture.

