#### Primary outcome

The primary outcome is the mean menstrual pain intensity change measured by visual analog scale (VAS) from baseline to 6 months. The VAS is a valid and reliable tool that has been widely used in various clinical trials involving patients with PD [27]. Participants will be asked to indicate a perception of pain intensity scored from 0 to 100 (0, no pain; 100, maximum).

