### Data collection and management

This trial mainly involved randomized group data, baseline data, post-intervention outcome data, follow-up data, and statistical analysis result data. Randomized group data are provided and managed by the investigator responsible for the random grouping of the trial. Baseline data, post-intervention outcome data, and follow-up data are collected by dedicated data collection researchers. Statistical analysis result data are collected and provided by the researcher in charge of data statistical analysis. In order to maximize the completeness of data collection, we will enhance communication with patients. We will strengthen our contact with patients by phone or social media to remind and monitor their medications, in addition to the face-to-face reminders at each visit. Free examinations and treatments are offered during the study, and visit times are flexible according to the patient’s schedule as far as possible. Furthermore, we will hold regular TCM health lectures at our clinical trial center to engage participants. All participants are assessed at baseline and 1, 2, 3, 4, 5, and 6 months after randomization. Work training will be held before the start of the project to provide detailed training and explanation of the trial protocol, standard operating procedures (SOPs) for study operations, and the content of case report forms (CRFs). Well-trained assessors, blinded to the treatment assignment, will use CRFs to collect clinical data at each visit. The person in charge of CRFs checks the daily completion and files the case report form in summary after standardization. Supervisors also should randomly check the CRFs at any time. Data will be recorded on the paper version of CRFs by designated outcome assessors and double entered in the electronic CRFs. Any incomplete data will be recorded as unknown, missing, or not applicable. All study-related information, such as participants’ medical records, will be kept securely in locked file cabinets with limited access. All private subject data are encrypted and protected, visible only to the project’s principal investigators, and used only for the research of the project. Principal investigators will be granted access to the cleaned dataset. To ensure confidentiality, data dispersed to project team members will be kept confidential to any identifiable participant information.

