### Data analysis

At the end of all measurements’ data collection, a skilled statistician blinded to group allocation will be performed by SPSS Statistics for Windows, version 22.0 (SPSSInc., Chicago, III., USA). We will descriptively summarize patient characteristics, outcome variables, and adverse events. Continuous variables, such as age and disease course, will be presented as mean ± standard deviation (*SD*) and analyzed by an independent-sample *T*-test. Quantitative variables such as baseline variables of socio-demographic data will be analyzed using *χ*^2^ or Mann-Whitney *U* tests. The repeated measurement variables, such as the primary and second outcomes, are analyzed by repeated-measures analysis of variance (ANOVA) or generalized estimation equations (GEE).

Both the full analysis set (FAS) and the per-protocol analysis set (PPS) will be used simultaneously to evaluate the effect and safety of GFW for PD. The FAS is for all participants who complete randomization and are assigned to receive treatment. The PPS is for the individuals who receive the assigned treatment according to the protocol and complete the entire study. For missing data, we will use the last-observation-carried-forward method. Although no interim analysis of outcomes is planned, a summary of the enrolment progress, AEs, and protocol deviations will be provided to the data monitoring committee (DMC) members. The trial should be terminated if there is clear evidence that SAEs are associated with the intervention or develop a serious illness. Statistical significance will be set at *P* < 0.05.

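### Feeling no better is a stated ground for leaving the trial, and nothing provides for collecting the 6-month VAS from women who leave for it, so that value may be lost in a way tied to the outcome

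*Protocol article*

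**What the plan says.** All references are to the protocol article.

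- **Interventions, last paragraph.** On lack of benefit: "Participants are free to withdraw from the trial if they feel they are not getting better". The next sentence covers safety and is worded differently: "if they develop a serious illness or a serious adverse event related to the study, allocated interventions will discontinue". The first concerns leaving the trial, the second stopping the treatment.
- **Primary outcome.** "The primary outcome is the mean menstrual pain intensity change measured by visual analog scale (VAS) from baseline to 6 months".
- **Design and setting.** "The total observation period will be 7 months, including a 1-month baseline period, a 3-month treatment period, and a 3-month follow-up period". Pain diaries run for the whole trial.
- **Data collection and management.** "All participants are assessed at baseline and 1, 2, 3, 4, 5, and 6 months after randomization". The section also lists retention measures: phone and social-media contact, reminders, free examinations and flexible visit times. None is directed at women who have stopped early.
- **Data analysis.** "The FAS is for all participants who complete randomization and are assigned to receive treatment". The per-protocol set requires completion of the entire study. Last observation carried forward (LOCF) is the only method named for missing values.

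**The concern.** The article has words for stopping treatment and uses them for safety events. For lack of benefit it speaks of leaving the trial. The ground for leaving is a woman's own view that her pain has not improved, which is very nearly what the VAS measures. If she acts on it, whether her 6-month value is missing depends on the outcome. If GFW works, it also depends on the arm, because more placebo women would feel no benefit.

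A woman in continuing pain also has a motive to leave. The Interventions section advises against NSAIDs and oral contraceptives for dysmenorrhea through follow-up, and mentions alternative treatments only for women who have completed the trial without remission.

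Neither analysis set would then hold her real 6-month pain. In the full analysis set it would be an earlier score carried forward; the per-protocol set would exclude her. The VAS is a self-rated score that does not require taking the granules, so stopping them need not end observation.

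**Working it through.** **Inputs from the Sample size section.** Planned difference 1, SD 1.67, 64 women per group, 10% dropout. Results below are given as a share of the planned difference, so the unit of the VAS does not matter.

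**The plan's own figures.** Per group, n = 2 × (1.960 + 1.282)² × 1.67² / 1² = 58.6, against the stated 58. This uses two-sided 0.05; the stated two-sided 0.025 would need 70 per group, a separate matter that does not affect this point. Dropout: 116 × 1.10 = 127.6, i.e. 128 as stated (116 / 0.90 = 128.9 by division). Ten per cent of 128 is about 13 women. The allowance replaces the number lost; it does not address who is lost.

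**Timing.** Granules end after three cycles and the endpoint is at month 6. If a woman's last score is from month 1 or 2, LOCF carries it over 5 or 4 months, from the treatment period into a period when no one is on granules.

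**Observed-case shift, simple form.** Suppose leavers' improvement is k SD worse than stayers' in each arm, and a share p leaves. The stayers' mean then exceeds the arm's true mean by p × k × SD, so the observed difference falls by (p_placebo − p_GFW) × k × SD. Both p and k are assumptions:

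| p placebo | p GFW | k | shift | share of planned difference |
|---|---|---|---|---|
| 0.15 | 0.05 | 1 | 0.10 × 1.67 = 0.167 | 17% |
| 0.20 | 0.05 | 1 | 0.15 × 1.67 = 0.25 | 25% |
| 0.15 | 0.05 | 0.5 | 0.084 | 8% |
| 0.20 | 0.05 | 0.5 | 0.125 | 13% |

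The average dropout in these rows is 10-12.5%, close to the plan's 10%.

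**Observed-case shift, selection form.** Assume improvement is normal with mean 1 on placebo and 2 on GFW, SD 1.67, true difference 1. Women improving by less than a threshold leave with a given probability (simulation, 2,000,000 per arm):

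| threshold | probability of leaving | loss placebo | loss GFW | observed difference |
|---|---|---|---|---|
| 0.5 | 0.10 | 3.8% | 1.8% | 0.98 |
| 0.5 | 0.25 | 9.5% | 4.6% | 0.94 |
| 0.5 | 0.50 | 19.0% | 9.2% | 0.85 |
| 1.0 | 0.10 | 5.0% | 2.7% | 0.99 |
| 1.0 | 0.25 | 12.5% | 6.9% | 0.96 |
| 1.0 | 0.50 | 25.0% | 13.7% | 0.88 |

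The shift is 1-15%. If every such woman left, the difference would fall to 0.52 or 0.44, but with 38-50% loss on placebo. That is far from the planned 10%, so I set it aside.

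**Under LOCF.** Let d be the mean of carried-forward improvement minus true month-6 improvement among leavers. The error in the difference is p_GFW × d_GFW − p_placebo × d_placebo. The documents give no value for d, and the sign can go either way: it depends on how pain moves between the last visit and month 6 in each arm.

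**The case against.** The strongest reply is that this is silence in a condensed article. The sentence mainly states a participant's freedom to leave, all participants are scheduled to month 6, and the full protocol may say more. Part of this stands: the loss is a possibility, not a stated rule against collection. But the sentence is not mere silence. It names lack of benefit as a ground for leaving the trial, next to a sentence that stops only the intervention.

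Four stronger readings are tempting and not supported:

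- **That no outcome is collected once the granules stop.** Months 4, 5 and 6 are off-granule assessments for all participants, and diaries continue.
- **That the safety clause ends follow-up.** It says only that "allocated interventions will discontinue".
- **That the full analysis set is contradicted.** LOCF keeps withdrawn women in it. The weakness is reliance on carried-forward scores.
- **That 17-25% is the bias of the planned analysis.** That range is for observed women only, on assumed dropout. LOCF carries a poor score forward and so keeps much of the non-response.

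It also stands that the likely direction is conservative for an observed-case comparison, and that likelihood or multiple-imputation methods could recover the comparison if leaving depended only on recorded monthly pain. Neither removes the case for collecting the values. LOCF is the method named, and dependence on unrecorded pain cannot be recovered by imputation under missing at random.

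**Conclusion.** The point holds in a limited form. The article makes feeling no better a reason to leave the trial, does not separate this from stopping the granules, and provides nothing for women who leave on that ground. Their 6-month VAS may be lost in a way that depends on the outcome and possibly on the arm.

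The size cannot be fixed from the documents. Taking both illustrations together, an observed-case comparison shifts by roughly 1-25% of the planned difference, toward no difference if more placebo women leave. This rests on assumed dropout rates by arm and an assumed gap between leavers and stayers. The planned LOCF analysis would give a different figure of unknown sign. This is an inexpensive improvement worth making, not a demonstrated bias in the result.

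**What to change.** In the last paragraph of the Interventions section, separate stopping the granules from withdrawing from follow-up. State that:

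- a woman who stops the granules for any reason is asked to continue the diary, VAS and other scales through month 6, unless she withdraws consent to data collection;
- these observed values enter the full analysis set in place of carried-forward ones;
- the reason and date of any withdrawal are recorded on the case report form.

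The right to withdraw and all treatment-stopping rules stay as they are.

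The cost is some protocol and case report form wording and a few extra phone or diary contacts, on visits and diaries already planned. Some values after stopping will reflect other therapies and should be flagged as such.
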